### Identifying the knowledge-to-action gaps

The topic of our KT intervention is evidence-based osteoporosis management and fracture prevention strategies [21-27]. Previous research by our team indicates that many LTC providers are unaware of osteoporosis and fracture prevention best practices, or have concerns surrounding diagnosis and treatment in elderly patients [28,29]. Furthermore, as a recent survey of LTC Medical Directors and Directors of Nursing documented, barriers to fracture care were modifiable and could be overcome through education and changes to local care delivery systems [30]. Rather than focusing on individual providers, we propose a model that takes a more collective approach and emphasizes integrating evidence-based practices into care processes.

In addition to proper assessment of individuals at high risk for fracture [21], we are emphasizing the wide-scale implementation of adequate levels of vitamin D (≥800 IU/day) because it is a tolerable, low-cost intervention with strong evidence that it can prevent fractures and falls in LTC residents [22,24,26,27,31]. In an environmental scan of 15 LTC homes we conducted in 2008 (n = 3,132 residents), the overall rate of vitamin D use was 38% [32], and there was considerable variation between homes with rates ranging from 11 to 62%. Another study [33] we conducted using data collected via the Resident Assessment Instrument (RAI) 2.0 [34,35] found similar results.

We developed a multifaceted, interdisciplinary KT intervention to improve the use of evidence-based osteoporosis and fracture prevention practices in LTC homes. The current report outlines the research design and protocol for evaluating this KT intervention.

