#### Clinical

The primary clinical outcomes are the proportion of residents prescribed vitamin D ≥800 IU/day at 6 and 12 months. The secondary prescribing outcomes are the proportion of residents prescribed ≥500 mg/day of elemental calcium and the proportion of high risk residents (*i.e.*, those with a fracture or documented osteoporosis) prescribed an osteoporosis medication (oral and IV bisphosphonates, teriparatide, denosumab) at 6 and 12 months. Other secondary outcomes include the number of falls, hip fracture and all fracture (hip, wrist, spine, foot, humerus, ribs, clavicle, ankle, other) for the data collection periods (*i.e.*, three months of falls and fracture data collected three times during the study, see Figure 1).

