#### Randomization and consent

Stratified block randomization was used to randomly allocate LTC homes to the intervention or control arm of the study (recruitment is now closed). LTC homes were stratified based on home size and profit/non-profit. Profit status was taken into consideration because there is some evidence that the quality of care is higher in non-profit homes compared to for-profit homes [43-45]. The allocation sequence was computer generated using nQuery 6.0 software by an off-site research member who is not involved in the recruitment, enrollment of clusters, or data analysis. Once the appropriate representative from the home was consented, the independent member assigned intervention and control groups based on the sequence and notified the coordinating centre. Because the homes are not blinded to treatment arms, the homes were informed of their allocation.

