#### Post-study sustainability

The final phase of the knowledge to action (KTA) cycle [60] includes building sustainability mechanisms into the intervention. It is anticipated that implementation of osteoporosis best practices will continue through the work of each LTC home's internal champion, who will be provided with updated resources and support by a forum on our website (http://www.osteoporosislongtermcare.ca[54]). This will enable the internal champions to interact with each other and share successes and challenges. We will work with our partner pharmacy provider to distribute prescribing reports to LTC homes one year after completing the study. This feedback is important given the high turnover of residents in LTC resulting in a different cohort of residents and staff since the study began.

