#### Patient-level

Figure 2 provides an overview of the data collection time-line. De-identified clinical data including demographic, prescribing, and co-morbidities (from the Medication Administration Record) are collected from the pharmacy database by the Director of Systems Services at Medical Pharmacies ([name]).

Falls and fractures data for every resident are collected by a LTC staff member at each home for three-month periods at three times during the study (coinciding with prescribing data pulls, Figure 2). The information source used to populate the data collection spreadsheets may vary by LTC home and sources are documented by the study coordinator. With the recent wide-scale implementation of the RAI-2.0 assessments across Ontario LTC homes [34,35], future studies collecting information on falls and fracture data will likely use this as a data source. The RAI-2.0 is a standard assessment using common methodology and measures and is completed by trained assessors (typically within 14 days of admission and then on a quarterly basis).

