### Data analysis

#### Quantitative analysis

Data from the trial will be analyzed and reported in accordance with the CONSORT criteria [41,63,64]. The baseline characteristics will be reported as mean (standard deviation) or median (minimum, maximum) values for continuous variables and as counts (percent) for categorical variables. The primary feasibility outcomes will be analyzed using descriptive statistics expressed as percent and corresponding 95% confidence intervals (CI). Our primary analyses will be performed using the intention-to-treat principle. The generalized estimating equations (GEE) technique, assuming an exchangeable correlation structure [65], will be used to determine differences between groups for the proportion of residents prescribed vitamin D, calcium and other osteoporosis medication, and number of fractures or falls. The GEE method will take into account the clustered nature of the data, given that residents treated within a LTC home are expected to be similar or correlated (clustered variable will be the LTC home). For the model, the unit of analysis will be the resident and the unit of inference will be the home. There is an increased risk of imbalance at the resident-level because of the home-level randomization. Therefore, resident baseline characteristics that will be included in this analysis are: age, gender, co-morbidities, and the number of prescribed medications. Unadjusted and adjusted odds ratios (OR) and corresponding 95% CIs will be reported. All statistical analyses will be performed using the SAS/STAT 9.2 software package (SAS Institute Inc., Cary, NC, USA) with the criterion for statistical significance set at α ≤0.05.

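### The adjusted model omits baseline vitamin D prescribing: the analysis is valid, but a cheap gain in precision and protection against chance imbalance is left unused

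*Protocol article*

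**What the plan says.** The Quantitative analysis section plans a GEE with exchangeable correlation and the home as cluster. Its reason for adjusting is that "There is an increased risk of imbalance at the resident-level because of the home-level randomization", and it then states that the "resident baseline characteristics that will be included in this analysis are: age, gender, co-morbidities, and the number of prescribed medications". Both versions of the result are to be given: "Unadjusted and adjusted odds ratios (OR) and corresponding 95% CIs will be reported". Neither is named as primary.

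The Clinical outcomes section defines the endpoint as a level at follow-up, not a change: "The primary clinical outcomes are the proportion of residents prescribed vitamin D ≥800 IU/day at 6 and 12 months". Under Randomization and consent, "LTC homes were stratified based on home size and profit/non-profit"; prescribing level is not a stratification factor.

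On available data, the Patient-level section says that falls and fractures are recorded "at three times during the study (coinciding with prescribing data pulls, Figure 2". The Background reports from a 2008 scan of 15 homes that "there was considerable variation between homes with rates ranging from 11 to 62" percent.

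**The concern.** The clinical aim is to raise prescribing from where it stands, and homes plausibly differ widely in where they stand. The baseline value of an outcome is usually a useful predictor of its later value, and age, gender, co-morbidities and drug count are unlikely to capture a home's prescribing habit. With about 20 homes per arm, one arm can start several points ahead by chance, and nothing in the stratification, the outcome definition or the named covariates takes that out.

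Two things are at stake. The realized estimate may be shifted by part of a chance head start in either direction. The confidence interval will also be wider than it needs to be if homes tend to keep their rank over time.

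**Working it through.** **Inputs from the Sample size section.** 120 residents per home; 30% at baseline; rises of 20 and 5 points, hence 50% versus 35% at follow-up; ICC 0.10; two-sided 0.05; 18 homes and 2,160 residents per arm; stated power 82%. **From Study population:** 19 intervention and 21 control homes. **Assumed, because the article does not give it:** r, the correlation between a home's baseline and follow-up proportions, shown for 0.3, 0.5 and 0.7.

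**1. The plan's own power.** Design effect = 1 + 119 × 0.10 = 12.9. Effective n per arm = 2,160 / 12.9 = 167.4. Standard error of the difference = √[(0.50 × 0.50 + 0.35 × 0.65) / 167.4] = √(0.4775 / 167.4) = 0.0534. Power is 80.2% with unpooled variance and 79.6% with pooled variance under the null, within about 2 points of the stated 82%.

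**2. Chance imbalance at baseline.** Variance of a home's proportion = 0.30 × 0.70 × 12.9 / 120 = 0.02258, so the SD is 15.0 points. Standard error of the difference between arms = √[0.02258 × (1/19 + 1/21)] = 0.0476, or 4.8 points. The 95% range is 1.96 × 4.76 = ±9.3 points. The chance of a difference above 5 points either way is 2 × [1 − Φ(0.05 / 0.0476)] = 0.29; above 10 points it is about 0.04. The target effect is 15 points.

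As a rough plausibility check, a range of 11 to 62% over 15 homes implies an SD of about 51 / 3.47 = 14.7 points, in line with ICC 0.10. That scan counted any vitamin D use.

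**3. How much carries over.** If home-level spread is similar at both times, about r × d of a baseline difference d is expected to persist. For d = 5 points this is 1.5, 2.5 or 3.5 points at r = 0.3, 0.5 or 0.7.

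**4. Gain from adjusting.** Adding the home's baseline proportion multiplies the variance of the difference by about 1 − r². Risk-difference scale, 18 homes per arm, pooled-null power:

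| r | Variance factor | SE (points) | Power |
|---|---|---|---|
| not adjusted | 1 | 5.3 | 79.6% |
| 0.3 | 0.91 | 5.1 | 83.2% |
| 0.5 | 0.75 | 4.6 | 89.6% |
| 0.7 | 0.51 | 3.8 | 97.4% |

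**5. Simulation check.** Home-level data were simulated for 19 versus 21 homes with a true effect of 15 points, 2,000 trials per setting, and correlation of the underlying home rates set at 0.3, 0.5, 0.7 and 0.85. Averaged over all trials, both estimators centre on 15 points. Without baseline the SD is about 5.0 points throughout; with it, 5.0, 4.6, 3.9 and 3.1. In the roughly 15% of trials where the intervention arm starts more than 5 points ahead, the unadjusted estimate averages 17.1, 18.6, 20.3 and 21.2 points, against 15.0 to 15.1 with baseline in the model.

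**The case against.** The strongest reply is that nothing planned here is wrong. Randomization makes the estimator unbiased, the GEE interval already includes between-home variation, and the sample size already pays for it through the ICC. That stands. A reader might infer that the planned model would report a head start as treatment effect. The article does not support that reading: only part of a head start persists, it can fall either way, and error rates are preserved.

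A reader might also take 11 to 62% as the trial homes' starting range for this outcome. The scan dates from 2008, covered 15 homes, measured any vitamin D use without the 800 IU/day threshold, and preceded the provincial toolkit of 2009/2010. It supports between-home variation in general and no more.

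The size of the gain is uncertain. The article itself notes the "high turnover of residents in LTC resulting in a different cohort of residents and staff since the study began", and the intervention aims to change prescribing habits; both could lower r. At r = 0.3 little is gained. The precision figures are also on the risk-difference scale and do not transfer directly to the odds ratios that will be reported.

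The covariate list concerns resident characteristics, so it does not expressly exclude home-level terms, and an analysis plan not shown might add one. Still, the article states a covariate set and a reason for it, and a plan that follows it would carry the omission forward. That the baseline pull exists is an inference: three pulls with outcomes at 6 and 12 months imply one, and the first educational session already presents the previous month's prescribing in intervention homes. The figure that would confirm it is not shown.

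The pilot label does not dispose of the point. Vitamin D prescribing is a named primary outcome with its own power calculation and significance level.

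**Conclusion.** The point holds as an inexpensive improvement, not as an error. Under the plan's inputs there is a 29% chance that the arms differ by more than 5 points at baseline, and part of that difference would remain in the realized estimate, in either direction. Adjustment would cut the standard error of the effect from 5.3 points to between 5.1 and 3.8 for r from 0.3 to 0.7. The chance-imbalance figure rests on the 30% rate and ICC of 0.10 in the Sample size section. The gain rests on r, which is assumed, and on the risk-difference scale. The point applies to both reported odds ratios, since neither contains baseline prescribing and neither is designated primary. Bias on average, or an invalid test, should not be read into it.

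**What to change.** In the Quantitative analysis section, add each home's baseline proportion of residents prescribed at least 800 IU/day, taken from the baseline pharmacy pull, as a covariate in the adjusted GEE at 6 and 12 months. Use the home-level value, because residents admitted after baseline have none of their own. Name this adjusted model as primary before the arms are compared; the Data monitoring section rules out any formal comparison until the end of the study, so this can still be prespecified. Do the same for calcium and for osteoporosis medication, each with its own baseline proportion.

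The cost is one or two sentences and one home-level degree of freedom, with no new data if the baseline pull exists as inferred. The adjusted odds ratio also becomes conditional on baseline prescribing and will generally differ from the unadjusted one even when the arms are balanced, so keep the unadjusted odds ratio beside it and say so in the report. If an analysis plan already contains such a term, aligning the two documents is enough.

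### Falls and fractures are defined as counts, but the only between-group measure the plan names is an odds ratio, which does not estimate a difference in number or rate

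*Protocol article*

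**What the plan says.** Under Study outcomes, Clinical, the article states: "Other secondary outcomes include the number of falls, hip fracture and all fracture". The period is given as "three months of falls and fracture data collected three times during the study". Under Data collection, Patient-level, these data are recorded for every resident by staff of the home.

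Under Data analysis, Quantitative analysis, one sentence says that GEE with an exchangeable correlation will be used for group differences in vitamin D prescribing, "calcium and other osteoporosis medication, and number of fractures or falls". The resident is the unit of analysis and the home is the cluster. The paragraph then names its only between-group measure: "Unadjusted and adjusted odds ratios (OR) and corresponding 95% CIs will be reported". It gives no rule for turning a count into a binary outcome, and no rate ratio or difference in means appears.

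**The concern.** The target and the measure do not match. The outcome section and the analysis section both speak of a number of events. The effect measure that follows belongs to a binary outcome.

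An analyst who follows the text has two courses. One is to reduce falls to any or none, so that a resident who falls five times counts the same as one who falls once. The other is to depart from the stated measure. The first silently changes the outcome, and the second leaves the choice to be made after the data are in.

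The stakes are moderate. The objectives speak only of documenting falls and fractures, but the analysis section goes further and compares the groups. The Discussion also offers effect sizes from this pilot as input for later trials, and an odds ratio for any fall cannot be used directly to plan a trial on fall rates.

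**Working it through.** **The plan's own figure.** None is given for falls or fractures. The only power figure (Sample size section) concerns vitamin D: 18 homes of 120 residents per arm, ICC 0.10, 82% power.
- Design effect: 1 + 119 × 0.10 = 12.9.
- Effective n per arm: 2,160 / 12.9 = 167.4.
- Power for 50% versus 35%, two-sided 0.05, unpooled variance: 80.2%, close to the stated 82%.

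Nothing below changes this figure.

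**Inputs for falls (assumed, because the documents give no rate).**
- Mean falls per resident per three-month window, λ: 0.3, 0.5 and 0.75. A value of 0.01 stands for a rare event such as fracture.
- Distribution: Poisson (dispersion d = 0), or negative binomial with d = 1 or d = 2.
- True rate ratio: 0.80, the same for all residents.

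**Formulas.**
- Poisson: P(any) = 1 − exp(−λ).
- Negative binomial: P(any) = 1 − (1 + dλ)^(−1/d).
- OR = odds of any fall at 0.8λ divided by odds of any fall at λ.

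**Odds ratio when the true rate ratio is 0.80.**

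| λ | Poisson | NB, d = 1 | NB, d = 2 |
|---|---|---|---|
| 0.01 | 0.799 | 0.800 | 0.801 |
| 0.3 | 0.775 | 0.800 | 0.817 |
| 0.5 | 0.758 | 0.800 | 0.825 |
| 0.75 | 0.736 | 0.800 | 0.832 |

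For falls (λ from 0.3 to 0.75) the range is 0.736 to 0.832. The OR can lie on either side of the rate ratio, depending on dispersion. At λ = 0.01 the two agree.

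**How much is discarded.** The share of falls that are repeats is 1 − P(any)/λ.
- λ = 0.5, d = 2: P(any) = 1 − 2^(−0.5) = 0.293. Falls per faller = 0.5 / 0.293 = 1.71. Repeats = (0.5 − 0.293) / 0.5 = 41%.
- Lowest case in the falls range, λ = 0.3, Poisson: 1 − 0.259 / 0.3 = 14%.
- Highest case, λ = 0.75, d = 2: 1 − 0.368 / 0.75 = 51%.

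**Effect on repeat falls only.** Take 30% fallers in both arms, with 1.5 versus 2.0 falls per faller. The rates are 0.30 × 1.5 = 0.45 and 0.30 × 2.0 = 0.60, so the rate ratio is 0.75. The proportions of fallers are equal, so the OR is 1.00. A 25% reduction in falls would not be seen.

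**The case against.** The strongest reply is that the odds-ratio sentence was never meant for falls and fractures. It comes after a list made up mostly of prescribing proportions, for which it is right, and a journal article condenses. The paragraph states no distribution or link, so it does not literally prescribe logistic regression for a count. This has some force, but the sentence is not limited to prescribing and no other measure is offered. As written, the text pairs "and number of fractures or falls" with an odds ratio.

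A second reply is that an odds ratio can be had without dichotomising, from a cumulative-logit model on ordered counts. That is true, and it is why the point is put in terms of a standard odds ratio. The article gives no sign of intending such a model, and a cumulative odds ratio is still not a ratio of numbers or rates.

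A third reply concerns size. If an effect is spread evenly over residents, the odds ratio is not far from the rate ratio, and the complete miss needs an effect confined to repeat falls. The outcomes are secondary, in a pilot centred on feasibility. All of this stands.

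A reader might also infer that turnover biases the comparison, because the article mentions "high turnover of residents in LTC resulting in a different cohort of residents and staff since the study began". The documents do not support this. The remark explains why prescribing reports will be sent one year after the study. It gives no rate of loss within a three-month window, and nothing suggests that turnover differs between the randomised arms. Nor is the lack of an offset an error in itself, since an article commonly leaves that to the analysis plan.

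**Conclusion.** The point holds as a mismatch in the stated text: a count outcome is paired with a measure that does not estimate it. It should be corrected, but it does not threaten the trial's main conclusions. The vitamin D analysis, for which an odds ratio suits a proportion, and the sample size are untouched.

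The practical consequence is for falls. Under the assumed rates and distributions, a uniform rate ratio of 0.80 would be reported as an odds ratio of about 0.74 to 0.83, and between 14% and 51% of falls would be discarded as repeats. In the extreme case of an effect on repeat falls alone, the odds ratio would be 1.0. These sizes rest entirely on assumed rates. For rare fractures the numerical difference is negligible. No claim is made about the direction or size of any bias from unequal time at risk.

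**What to change.** Restrict the odds-ratio sentence to the prescribing proportions. Add a sentence stating that numbers of falls and fractures will be compared by GEE with a log link and count (Poisson or negative binomial) variance, clustered by home, and reported as unadjusted and adjusted rate ratios with 95% CIs. Include log time at risk in the window as an offset where resident dates are available, and home census or bed-days otherwise.

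If the investigators do want any fall or any fracture as the outcome, they can keep the odds ratio, but the outcome section must then define it that way.

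The cost is a second model statement, with no change to the sample size. The denominator may not be free. The article lists demographic, prescribing and co-morbidity data and the homes' falls and fracture spreadsheets, but no admission, discharge or death dates, so exposure may have to be requested from the homes or the pharmacy.

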#### Qualitative analysis

All interview data will be audiotaped and then transcribed verbatim by a professional transcriber. Data analysis will take place concurrently with data collection so that any emerging themes can be incorporated into the interview guide and the codebook. To ensure that we reach informational saturation (all emerging themes are well understood and supported by ample data), any topics that are still unclear after completing the interviews will be revisited in brief telephone conversations with interviewees from LTC homes that provided the least amount of information on those particular topics. A qualitative data management and retrieval software program (QSR-Nvivo) [66] will be used to assist with data organization and retrieval during thematic framework analyses. Both the development of the interview guides and the thematic analyses applied to the transcripts will be guided by two theories that address the change process at the individual and organizational levels: the Theory of Planned Behaviour [67,68], and the Diffusion of Innovations [69-71].

